##### *Mediator analyses*

If MBSR or CBT is found to be effective (relative to usual care and/or to each other) in improving either primary outcome at 26 or 52 weeks, we will move to aim 3 to identify the mediators of the effects of MBSR and group CBT on the RDQ and pain bothersomeness scale. We will perform the series of mediation analyses separately for the two primary outcomes (RDQ and pain bothersomeness scale scores) and for each separate treatment comparator of interest (usual care versus CBT, usual care versus MBSR and CBT versus MBSR). We will conduct separate mediator analyses for the 26- and 52-week outcomes (if MBSR or CBT is found to be effective at those time points).

Next, we describe in detail the mediator analysis for the 26-week time point. A similar analysis will be conducted for the 52-week time point. We will apply the framework of the widely used approach of Baron and Kenny [91]. Once we have demonstrated the association between the treatment and the outcome variable (the “total effect” of the treatment on the outcome), the second step will be to demonstrate the association between the treatment and each putative mediator. We will construct a regression model for each mediator with the 4- or 8-week score of the mediator as the dependent variable and the baseline score of the mediator and treatment indicator as independent variables. We will conduct this analysis for each potential mediator and will include as potential mediators in the following step only those that have a P-value ≤0.10 for the relationship with the treatment. The third step will be to demonstrate the reduction of the treatment effect on the outcome after removing the effect of the mediators. We will construct a multimediator inverse probability weighted (IPW) regression model [92]. This approach will allow us to estimate the direct effects of treatment after rebalancing the treatment groups with respect to the mediators. Specifically, we will first model the probability of the treatment effects, given the mediators (that is, all mediators that were found to be associated with treatment in step 2), using logistic regression and adjusting for potential baseline confounders. Using this model, we will obtain the estimated probability that each person received the observed treatment, given the observed mediator value. We will then use an IPW regression analysis to model the primary outcomes on treatment status while adjusting for the baseline levels of the outcome and mediator. Comparing the weighted model with the unweighted model will allow us to estimate how much of the direct effect of treatment on the associated outcome can be explained by each potential mediator. The inclusion in step 3 of all mediators found to be significant in step 2 will enable us to examine whether the specific variables that we hypothesized would differentially mediate the effects of MBSR versus CBT in fact mediate the effects of each treatment independently of the effects of the other “process variables”.

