### Specific aims

Our specific aims and their corresponding hypotheses are outlined below.

1. To determine whether MBSR is an effective adjunct to usual medical care for persons with CLBP

*Hypothesis 1*: Individuals randomized to the MBSR course will show greater short-term (8 and 26 weeks) and long-term (52 weeks) improvement in pain-related activity limitations, pain bothersomeness and other health-related outcomes than those randomized to continued usual care alone.

2. To compare the effectiveness of MBSR and group CBT in decreasing back pain–related activity limitations and pain bothersomeness

*Hypothesis 2*: MBSR will be more effective than group CBT in decreasing pain-related activity limitations and pain bothersomeness in both the short term and long term. The rationale for this hypothesis is based on (1) the modest effectiveness of CBT for chronic back pain found in past studies, (2) the positive results of the limited initial research evaluating MBSR for chronic back pain and (3) growing evidence that an integral part of MBSR training (but not CBT training)—yoga—is effective for chronic back pain.

3. To identify the mediators of any observed effects of MBSR and group CBT on pain-related activity limitations and pain bothersomeness

*Hypothesis 3a*: The effects of MBSR on activity limitations and pain bothersomeness will be mediated by increases in mindfulness and acceptance of pain.

*Hypothesis 3b*: The effects of CBT on activity limitations and pain bothersomeness will be mediated by changes in pain-related cognition (decreases in catastrophizing, beliefs that one is disabled by pain and beliefs that pain signals harm, as well as increases in perceived control over pain and self-efficacy for managing pain) and changes in coping behaviors (increased use of relaxation, task persistence and coping self-statements and decreased use of rest).

4. To compare the cost-effectiveness of MBSR and group CBT as adjuncts to usual care for persons with chronic back pain

*Hypothesis 4*: Both MBSR and group CBT will be cost-effective adjuncts to usual care.

We will also explore whether certain patient characteristics predict or moderate treatment effects. For example, we will explore whether patients with higher levels of depression are less likely to improve with both CBT and MBSR or whether such patients are more likely to benefit from CBT than from MBSR (that is, whether depression level is a moderator of treatment effects).

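### The joint mediator weighting gives one combined figure, so when several mediators pass the screen it cannot show what each explains or separate Hypothesis 3a from 3b

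*Protocol article*

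**What the plan says.** The Mediator analyses section of the protocol article sets out three steps, run separately by primary outcome, treatment pair and time point (26 and 52 weeks).

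- **Step 1** shows that treatment affects the outcome, which the section calls the total effect.
- **Step 2** regresses each mediator, one at a time, on treatment and its own baseline value. Only mediators with P ≤0.10 go forward.
- **Step 3** is the attribution step: "We will construct a multimediator inverse probability weighted (IPW) regression model". Treatment is modelled "given the mediators (that is, all mediators that were found to be associated with treatment in step 2), using logistic regression". The weights are then used to "model the primary outcomes on treatment status while adjusting for the baseline levels of the outcome and mediator".

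Two properties are claimed for step 3. The weighted-versus-unweighted comparison is said to "estimate how much of the direct effect of treatment on the associated outcome can be explained by each potential mediator". Including all selected mediators is said to show whether the hypothesized variables "in fact mediate the effects of each treatment independently of the effects of the other" process variables.

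Under Specific aims, Hypothesis 3a reads: "The effects of MBSR on activity limitations and pain bothersomeness will be mediated by increases in mindfulness and acceptance of pain". Hypothesis 3b names pain-related cognitions and coping behaviors for CBT. The section on measures used in mediator analyses adds that all potential mediators will be explored in both treatment groups.

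**The concern.** In step 3 the post-randomization mediators enter only through the weight. Each participant has one weight, built from "all mediators that were found to be associated with treatment in step 2". The outcome model has a treatment term and baseline terms, but no coefficient for any post-randomization mediator. The only output that bears on mediation is therefore the difference between two treatment coefficients, and that is a single number for the whole selected set. Putting all the mediators into one weight does not show their independent roles; it merges them.

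Hypotheses 3a and 3b say which variables carry which treatment's effect. Because all mediators are candidates for every comparison, the selected set may mix MBSR-type and CBT-type variables. A clear joint result would then fit 3a, 3b or both, and a statement that one set was responsible would have no support in the analysis.

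The wording also slips on the quantity being explained. The weighted model estimates the direct effect, as the section itself says a few sentences before. What mediators explain is the part of the total effect that weighting removes.

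**Working it through.** The plan gives no figure to reproduce, so the described procedure was worked through algebraically and simulated.

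**Inputs from the protocol.** One logistic model for treatment on all selected mediators; outcome regressed on treatment with those weights; comparison with the unweighted fit. The sample size section gives 88 analysable participants per group, so 2 × 88 = 176 per treatment pair.

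**Assumptions not in the protocol.** Two mediators M1 and M2, each shifted by a = 0.5 SD by treatment, so both would pass step 2 in a large sample. Mediator-to-outcome slopes b1 and b2, direct effect c = −1, correlation ρ between mediator errors of 0 or 0.5. Baseline covariates were left out for simplicity.

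**Formulas under this linear set-up.**
- Total effect = c + a·b1 + a·b2
- Explained jointly (total minus jointly weighted) = a·(b1 + b2)
- M1 entered alone: a·b1 + ρ·a·b2
- M1 by leave-out (change when M1 is dropped from the joint model) = joint minus M2 alone = a·b1·(1 − ρ)

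The joint figure depends only on the sum b1 + b2. With (b1, b2) = (−2, 0), (0, −2) or (−1, −1) it is 0.5 × (−2) = −1 each time.

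**Simulation, n = 400,000 per scenario** (paired values are M1 / M2):

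| ρ | True carrier | Joint | Entered alone | Leave-out |
|---|---|---|---|---|
| 0 | M1 only | −0.99 | −0.99 / 0.00 | −0.99 / 0.00 |
| 0 | M2 only | −1.01 | 0.00 / −1.01 | 0.00 / −1.01 |
| 0 | Equal split | −1.00 | −0.50 / −0.50 | −0.50 / −0.50 |
| 0.5 | M1 only | −1.01 | −1.01 / −0.51 | −0.50 / 0.00 |
| 0.5 | M2 only | −1.01 | −0.50 / −1.01 | 0.00 / −0.51 |
| 0.5 | Equal split | −1.01 | −0.76 / −0.76 | −0.25 / −0.25 |

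**At the planned size** (n = 176, 1000 runs, ρ = 0), the mean joint figure was −1.00, −0.99 and −0.99 for the three cases, with SD 0.33, 0.32 and 0.24.

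**Reading the table.** The joint column does not distinguish the three cases at either correlation. The entered-alone column does so cleanly only at ρ = 0. At ρ = 0.5 it credits M2 with −0.51 when M2 mediates nothing (formula: 0.5 × 0.5 × (−2) = −0.50). Leave-out gives the non-mediator 0.00, but gives the true mediator only −0.50 of its −1 (formula: 0.5 × (−2) × 0.5 = −0.50).

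**The case against.** A reader might infer that the mediation plan cannot address Hypotheses 3a and 3b at all. The protocol does not support that. Step 2 tests each mediator separately for each comparison and drops those with P >0.10, so some attribution takes place before any weighting. If only mindfulness and acceptance pass for MBSR versus usual care, the joint figure is the set-level quantity that 3a asks about; the same holds for 3b. The insensitivity shown above applies only among mediators that pass, and the simulation covers only that case. This part of the objection stands and limits the point.

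A second argument is that parts of the section use the singular for the mediator, which could hint at one-at-a-time fits that are poorly described. The parenthesis defining the weight model and the section's last sentence both describe a joint model, so the singular does not settle it. At best the text contradicts itself.

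Third, the cited method paper or an analysis plan not shown may contain a decomposition. That cannot be checked. The article says it describes the analysis in detail, gives no decomposition, and makes a positive claim that the described comparison cannot meet. The point is that claim, not an omitted detail.

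Finally, Aim 3 is reached only if a treatment proves effective, and the Abstract and Discussion speak of exploring mediators. No primary efficacy conclusion depends on it. That bears on weight, but Aim 3 is still a numbered aim with specific hypotheses.

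**Conclusion.** The point holds in a bounded form. As written, step 3 estimates the part of the total treatment effect explained jointly by the mediators that pass step 2. It does not give a share for each mediator, and it does not show that one set acts independently of another. The gap arises when more than one mediator passes, and matters most when MBSR-type and CBT-type mediators both pass. When only one set passes, the joint figure is informative for that set as a whole.

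That the joint figure cannot be apportioned follows from the procedure; the sizes quoted rest on the assumed effects and correlations. It would also go too far to infer that refitting with one mediator or set at a time settles the matter: that works only when mediators are uncorrelated, and the protocol gives no correlations. The primary efficacy analyses are unaffected. The correction should be made, because it removes a property wrongly claimed for a stated aim.

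**What to change.** 1. Reword the attribution sentence so that the weighted-versus-unweighted comparison estimates how much of the *total* effect is explained by the selected mediators *jointly*.
2. Then either drop the claim of independent mediation, or define a set-specific quantity before results are seen. For the second option:
   - Use three pre-named sets: mindfulness and acceptance; pain beliefs and appraisals; coping. Restrict each to the members that pass step 2.
   - Take as the measure of independent mediation the change in the weighted treatment effect when that set is left out of the joint model, with a bootstrap confidence interval.
   - Report the set entered alone only as a descriptive companion, because with correlated sets it can credit one that mediates nothing.

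**Cost.** No new data. Three sets, each left out and entered alone, make 3 × 2 = 6 extra fits. Over 3 comparisons, 2 outcomes and 2 time points that is up to 6 × 3 × 2 × 2 = 72 weighted models, each bootstrapped if the companion fits also carry intervals. Intervals will be wide, set-specific parts need not add up to the joint figure, and the leave-out measure understates a set's full share when sets are correlated. Dropping the independence claim costs only the rewording, but then 3a and 3b cannot be separated whenever both kinds of mediator pass.

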#### Cost-effectiveness analyses

A societal perspective cost–utility analysis (CUA) will be performed to compare the incremental societal costs revealed for each treatment arm (direct medical costs paid by GHC and the participant plus productivity costs) to incremental effectiveness in terms of change in participants’ QALYs [93]. This analysis will be possible only for study participants recruited from GHC. This CUA can be used by policymakers concerned with the broad allocation of health-related resources [94,95]. For the payer perspective, direct medical costs (including intervention costs) will be compared to changes in QALYs. This CUA will help us to determine whether it makes economic sense for MBSR to be a reimbursed service among this population. A bootstrap methodology will be used to estimate confidence intervals [96]. In secondary analyses conducted to assess the sensitivity of the results to different cost outcome definitions, such as varying assumptions of wage rates used to value productivity and the inclusion of non-back-related health-care resource utilization [97] in the total cost amounts, will also be considered. In cost-effectiveness analyses, we will use intention to treat and adjust for health-care utilization costs in the one calendar year prior to enrollment and for baseline variables that might be associated with treatment group or outcome, such as medication use, to control for potential confounders. We expect there will be minimal missing data, but sensitivity analyses (as described above for the primary outcomes) will also be performed to assess cost measures.

## Discussion

In this trial, we will seek to determine whether an increasingly popular approach for dealing with stress—mindfulness-based stress reduction—is an effective and cost-effective treatment option for persons with chronic back pain. Because of its focus on the mind as well as the body, MBSR has the potential to address some of the psychosocial factors that are important predictors of poor outcomes. In this trial, we will compare the effectiveness and cost-effectiveness of MBSR with that of CBT, which has been found to be effective for back pain but is not widely available. The study will also explore psychosocial variables that may mediate the effects of MBSR and CBT on patient outcomes. If MBSR is found to be an effective and cost-effective treatment option for persons with chronic back pain, it will be a valuable addition to the treatment options available for patients with significant psychosocial contributors to this problem.

## Trial status

Recruitment started in August 2012 and was completed in April 2014.

## Abbreviations

AE: Adverse event; CAM: Complementary and alternative medicine; CATI: Computer-assisted telephone interview; CBT: Cognitive-behavioral therapy; CLBP: Chronic low back pain; CUA: Cost–utility analysis; DSMB: Data and Safety Monitoring Board; GHC: Group Health Cooperative; ICD-9: International *Classification of Diseases Ninth Revision*; IPW: Inverse probability weighting; IRB: Institutional Review Board; MBSR: Mindfulness-based stress reduction; NCCAM: National Center for Complementary and Alternative Medicine; QALY: Quality-adjusted life-year.
